## Methods/Design

### Study design

Smart Moms is a two-group randomized controlled trial designed to test the efficacy of a 6-month program to reduce SSB and juice consumption among children ages 3–5 of mothers who are overweight or obese compared to a waitlist control group. Mother-child dyads were randomly assigned to the Smart Moms intervention group or to a waitlist control group after baseline data were collected. Randomization was stratified by two factors: whether or not the child was in childcare/kindergarten and child baseline SSB/juice intake. The primary hypothesis is that the Smart Moms program will result in a greater reduction in child fluid ounces of SSBs and juice compared to the control group at 6 months. Secondary outcomes include maternal percent weight loss, maternal caloric beverage consumption, and child BMI z-score at 6 months. The study was approved by the UNC non-biomedical IRB on March 18, 2014.

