### Sample size and statistical analysis

The primary outcome for the study was change in child SSB/juice intake in fluid ounces from baseline to 6 months. Based on evidence from three previous studies that resulted in significant SSB/juice reductions in children [14, 29, 30], the study was powered to detect a difference of a 6-oz reduction between groups at 6 months, with a within-group standard deviation of 6.0. Therefore, with 80 % power at an alpha level of .05 and accounting for 20 % attrition, the study required 21 participants per group for a minimum of 42 total participants to detect a significant difference in SSB/juice reduction.

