### Data analysis

SAS version 9.3 (Cary, NC) will be used to conduct statistical analyses for the primary and secondary analyses of this intervention. Intent-to-treat analyses using linear mixed models will be used to examine changes in the primary and secondary outcomes. The linear mixed models will include a random intercept and effects for treatment group, time, and group by time interactions for both follow-up visits. A Bonferroni adjustment will be used to account for the effect of comparisons at multiple time points. Any characteristics found to be associated with both treatment group and the outcomes will be defined as confounders and will be included as covariates in analyses.

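### The 6-month primary comparison is sized at alpha .05, but the analysis section applies a Bonferroni adjustment over time points without exempting it; if that covers both follow-up visits, planned power is about 71%, not 80%

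*Protocol article*

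**What the plan says.** The Study design section gives one primary hypothesis, that the program produces a "greater reduction in child fluid ounces of SSBs and juice compared to the control group at 6 months". The sample size section matches it: "The primary outcome for the study was change in child SSB/juice intake in fluid ounces from baseline to 6 months". The planning figures there are:

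- Difference: "the study was powered to detect a difference of a 6-oz reduction between groups at 6 months".
- Spread: "with a within-group standard deviation of 6.0".
- Error rates and dropout: "with 80 % power at an alpha level of .05 and accounting for 20 % attrition".
- Result: "the study required 21 participants per group for a minimum of 42 total participants".

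No allowance for multiple comparisons appears in that section. The Measures section schedules two post-baseline assessments, at 3 and 6 months. The Data analysis section describes linear mixed models for the primary and secondary outcomes, with group-by-time terms at each of these visits, and then adds: "A Bonferroni adjustment will be used to account for the effect of comparisons at multiple time points". It gives no divisor and no per-comparison alpha, and it does not set the 6-month primary contrast apart.

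**The concern.** One outcome compared once, at 6 months, is a single test, and the trial was sized for that test at the full .05. Read as written, the analysis section puts the same test into a family of visit comparisons and so lowers its threshold. The two sections then use different error rates for one comparison.

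Two things are at stake. First, the stated 80% power would not be what the plan's own analysis rule gives, in a trial planned for as few as 42 dyads. Second, the success criterion is ambiguous: a 6-month p-value between .025 and .05 would count as a success under the sample size section and as a failure under the analysis section. An ambiguity of that kind should not remain open until the results are known.

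**Working it through.** **Inputs.** All are from the protocol article. Sample size section: difference 6 oz, SD 6.0 (standardised effect 6/6 = 1), alpha .05, power 80%, attrition 20%, 21 per group. Measures and Data analysis sections: two follow-up visits. Inferred: two-sided testing, and a Bonferroni divisor of two.

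**Formula.** Two-sample t-test with n completers per group. The noncentrality is 6 / (6 × √(2/n)) = √(n/2), with 2n − 2 degrees of freedom. Power is the probability that the noncentral t exceeds the two-sided critical value in absolute size.

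**Step 1: reproduce the stated sample size.** At two-sided .05 the smallest n with at least 80% power is 17 per group (power 80.7%). Adding 20% gives 17 × 1.2 = 20.4, rounded up to 21. Dividing by 0.8 gives 21.25, which is 21 rounded or 22 rounded up. The normal approximation gives 16 completers and 16 / 0.8 = 20. The stated 21 is therefore reproduced to within rounding. A one-sided .05 test needs only 13 to 14 completers, or 16 to 18 enrolled, and does not reproduce 21. The sample size therefore appears to rest on an unadjusted two-sided .05.

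**Step 2: apply the Bonferroni split.** Two visits give .05 / 2 = .025 per comparison. Expected completers are 21 × 0.8 = 16.8 per group, and the noncentrality is √8.4 = 2.90.

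| Completers per group | Method | Power at .05 | Power at .025 |
|---|---|---|---|
| 16 | t-test | 78.1% | 68.0% |
| 16.8 | t-test | 80.2% | 70.6% |
| 17 | t-test | 80.7% | 71.2% |
| 16 | normal approximation | 80.7% | 72.1% |
| 17 | normal approximation | 83.0% | 75.0% |
| 21 (no attrition) | t-test | 88.5% | 81.5% |

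At 16.8 completers the type II error rises from about 20% to about 29%.

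**Step 3: express it as a difference.** With 16.8 completers per group, the difference detectable with 80% power is 5.98 oz at .05 and 6.65 oz at .025.

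**Step 4: the sample size that would hold 80% at .025.** The t-test needs 21 completers per group (20 give 79.3%). Allowing for attrition, 21 / 0.8 = 26.25, so 27 per group or 54 in total. With the × 1.2 convention it is 25.2, so 26 per group or 52 in total.

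**Sensitivity to the divisor.** If three comparisons were in the family (.05 / 3), power at 16.8 completers would be 64.5%.

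**The case against.** The strongest reply is that the analysis section never says the primary contrast is tested at .025. It states neither a divisor nor a family of comparisons. The Bonferroni sentence may have been meant for visit-by-visit comparisons in general, with the single 6-month contrast left at .05, and a condensed article can leave the exact allocation to an analysis plan that is not shown. This stands in part. A reader might infer that the trial's power simply is 71%, but the documents support that only conditionally. The mismatch itself remains: the adjustment is stated for models that include the primary outcome, no exemption is given, and the sample size makes no allowance for it.

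A second reply is that 71% assumes enrolment at the stated minimum and the full 20% attrition. With no attrition, power at .025 is 81.5%. The mixed model also uses dyads who have a 3-month value but no 6-month value, which may add some precision. Both points are fair. However, the plan itself assumes 20% attrition, and its sample size counts on neither extra enrolment nor a gain from the model.

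A third reply is that Bonferroni is merely conservative. That is correct, and it limits the severity. A reader might infer that the adjustment is an error to be removed, or that it undermines a positive result. The documents support neither. Correcting over two visits is a legitimate way to allow a claim at either one, and it neither inflates type I error nor biases the estimate. Removing it also has a cost: the article reports recruitment and assessments in the past tense, so relaxing a published threshold after outcome data have been seen would not be sound.

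**Conclusion.** The point holds in conditional form. The sample size section and the Data analysis section do not agree on the error rate for the 6-month primary comparison. If the Bonferroni adjustment covers the two follow-up visits, planned power is about 71% (68% to 75% over calculation variants) against the stated 80%, and the difference detectable with 80% power is about 6.65 oz.

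This rests on a divisor of two, read from the two follow-up visits in the model; a two-sided test, inferred because only that reproduces about 21 per group; enrolment at the stated minimum with 20% attrition; and the planning t-test, with no precision gain credited to the mixed model. The matter should be fixed but is not critical: the consequence is lost power and an unclear success threshold, not a false-positive risk.

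**What to change.** Reconcile the two sections in one of two ways.

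1. State in the Data analysis section that the single 6-month group-by-time contrast for child SSB/juice is tested at two-sided .05, and that the 3-month comparison is secondary, for example tested only if 6 months is significant. That sequence keeps the overall error rate over the two visits at 5%. This must be decided and recorded before any unblinded outcome data are examined. The price is that 3 months cannot be claimed if 6 months fails.
2. Keep the Bonferroni adjustment, state that it covers the primary contrast and with what divisor, and restate the power in the sample size section as about 71% under the planned attrition. The price is an openly lower power.

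If outcome data have already been seen, use the second option. Either change takes about one sentence and no additional participants. Holding 80% power at .025 instead would have meant about 26 to 27 dyads per group.

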### Measures

Participants completed assessments at baseline (prior to randomization), 3 months, and 6 months. Each assessment period included an in-person visit and the completion of online questionnaires. Participants in either treatment group who missed assessment visits were contacted frequently by phone and email to schedule and complete assessment visits. Participants received a $20 honorarium for completing each of the 3- and 6-month assessments, meaning participants who completed both assessments received $40 total.

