#### Social cognitive mediators

There are no existing validated questionnaires that measure theoretical constructs specific to parents reducing the SSB consumption of young children. Therefore, this study used a series of questions drawn from several previous research studies and developed specifically for use in this study. To assess self-efficacy for reducing their child’s SSB consumption and other behaviors, mothers completed six items from a previous study that assessed their confidence in making obesity-related changes with their children [38]. In the cited study, the items had high internal consistency (α = 0.72). An additional three items adapted from a previous study [39] were added to assess self-efficacy for making changes in the child’s SSBs and outcome expectations for limiting SSBs. Mothers’ frequency of setting limits with SSB consumption and other behaviors was assessed with nine items used and adapted from a previous study [40]. The questions assessed mothers’ agreement with restricting SSB/juice consumption, TV time, and fast food consumption.

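### Covariates are to be chosen by their observed association with arm and outcome, which is unsound in a randomised trial and, with no baseline restriction, would admit post-randomisation intervention targets

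*Protocol article*

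**What the plan says.** The Data analysis section specifies intent-to-treat linear mixed models with a random intercept, group, time, and group-by-time interactions at both follow-up visits. It then gives the covariate rule: "Any characteristics found to be associated with both treatment group and the outcomes will be defined as confounders", and these "will be included as covariates in analyses". It names no candidate variables, measurement time or threshold.

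Three other parts of the article bear on this rule.

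- **Design.** The Study design section states that "Smart Moms is a two-group randomized controlled trial", with allocation to intervention or "waitlist control group after baseline data were collected". It adds: "Randomization was stratified by two factors: whether or not the child was in childcare/kindergarten and child baseline SSB/juice intake".
- **Timing.** The Measures section says: "Participants completed assessments at baseline (prior to randomization), 3 months, and 6 months".
- **Intervention targets.** The Intervention section and its Table 1 list limit setting and the home environment among the things the programme tries to change. The Measures section has a subsection on social cognitive mediators, where mothers' "frequency of setting limits with SSB consumption and other behaviors was assessed with nine items", and another on the home environment.

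**The concern.** The rule comes from observational research, where an imbalance between groups may reflect how people came to be in them. Here allocation is random and follows baseline measurement. A baseline variable associated with arm is imbalanced by chance, and a later variable associated with arm may have been changed by the intervention. Neither is confounding at randomisation.

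Three consequences follow.

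- One of the two screens uses the outcomes, so nobody can write down the primary model before the results are known.
- Stratification balances childcare status and baseline intake across arms, so the variables the design treats as important are the least likely to pass the arm screen.
- A follow-up measure of something the intervention is meant to change, and through which it is meant to work, is expected to be associated with both arm and outcome. It therefore meets the rule's definition of a confounder. Adjusting for it removes part of the effect the trial sets out to estimate.

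**Working it through.** **Inputs from the article (Sample size and statistical analysis).** Difference 6 oz, SD 6.0, alpha .05 (two-sided assumed), power 80 %, attrition 20 %, 21 per group.

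**Plan's own figure.** By the normal formula, n = 2(1.96 + 0.84)² × (6/6)² = 15.7, so 16 per arm. The t-test needs 17. With attrition, 16/0.8 = 20, 17 × 1.2 = 20.4 (21), and 17/0.8 = 21.25 (22). The stated 21 reproduces. With 17 completers per arm, t-test power is 80.7 %. The checks below use 17 per arm.

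**A. Baseline variables in the planned model.** Group-by-time terms at both follow-up visits imply that baseline is the reference time. For dyad i at visit j:

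Y_ij = b0 + b1·G_i + b2·T3 + b3·T6 + b4·G_i·T3 + b5·G_i·T6 + γ·X_i + u_i + e_ij

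With complete data, b5 is the mean baseline-to-6-month change in the intervention arm minus that in the control arm. X_i is constant within a dyad and cancels from each change. In simulation with X deliberately imbalanced by 0.8 SD, fits with and without X differed by about 1e-13 oz, which is rounding error. With 21 per arm and 20 % missing at 6 months, the mean difference was −0.0003 oz and the largest in any one trial was 0.35 oz.

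**B. Baseline variables in a single-outcome regression.** Assumed: 10 candidates, joint R² .3, both screens at p < .10, true effect 6 oz.

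| Outcome screen | Mean estimate | Power |
|---|---|---|
| Arms pooled | 5.6–5.7 oz | 75 % |
| Within arm | 6.0 oz | 80–81 % |
| No adjustment | 6.0 oz | 80–81 % |

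The attenuation needs the pooled screen, in which a chance-imbalanced variable picks up the treatment effect and so appears related to the outcome. With no true effect, rejection rates were 2.7–4.9 % under pooled screens across the settings tried and about 5 % under the within-arm screen.

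**C. One post-randomisation variable.** Assumed: the intervention shifts the variable by 1 SD and half the effect runs through it.

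- Total effect = direct + (shift × slope): 6 = 3 + 1 × 3.
- Effect after adjustment = 6 − 1 × 3 = 3 oz.
- In general, if share s is mediated, 6(1 − s) remains: 4.5, 3.0 and 1.5 oz for s = 25, 50 and 75 %.

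The rule does not select the variable in every trial. With shifts of 0.8–1.2 SD and a .05 screen, it did so in 50–92 % of simulated trials in a single-outcome analysis. Averaged over all trials:

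| Mediated share | Mean estimate |
|---|---|
| 25 % | 4.6–4.9 oz |
| 50 % | 3.1–3.7 oz |
| 75 % | 1.7–2.5 oz |

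Power was 14–61 %, against about 80 % unadjusted. In the planned mixed model, adding such a time-varying variable at a 50 % share moved the average 6-month group-by-time estimate from 5.7 to 2.8 oz, again about half. The 5.7 here is the simulated unadjusted average; its match with the figure in B is a coincidence.

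**The case against.** The strongest reply is that the rule does little harm as the authors probably mean it. They call the selected variables confounders and describe the social cognitive constructs as mediators, so they know the difference. The term characteristics fits the demographics collected at baseline. On that reading check C falls away, and check A shows that a baseline main effect cannot move the primary estimate with complete data. Dropout can also create real imbalance among those observed, and candidate lists and thresholds commonly belong in an analysis plan that is not shown.

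Much of this stands. A reader might infer that the plan will adjust for mediators; the article does not say so, only that its wording would let them in. A reader might also infer that the rule biases the primary result toward zero even with baseline variables. That holds only for a single-outcome analysis with an arms-pooled screen, and the article specifies neither. Nor does the rule inflate type I error in the baseline checks. Finally, baseline intake is not lost if it happens to be balanced: it is already in the model if baseline is one of the response times.

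Two points survive. The article does not leave covariate choice open; it states a rule, and a threshold or candidate list added elsewhere would not stop selection from depending on outcomes. And screening on arm and outcome is not a method for handling attrition.

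**Conclusion.** The rule is unsound for this design and should be replaced. That covariates are chosen from observed outcomes, and that the rule works against the stratification, follows from the text without further assumption.

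The size of the harm depends on how the rule is applied. For baseline main effects in the planned model with complete data, the change in the 6-month estimate is nil. For a follow-up variable carrying half the effect, the estimate roughly halves and no longer measures the total intent-to-treat effect. The mediated share, the shift in the variable, the screening thresholds and the number of candidates are all assumptions, because the article gives none. That the targeted constructs are re-measured after randomisation is read from the general statement on assessments and online questionnaires; demographics are the only measure tied to baseline alone.

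Severity: should-fix. The serious consequence depends on a permissive reading that the authors may not intend.

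**What to change.** - Delete the association-based rule.
- Pre-specify adjustment for the two stratification factors. Enter childcare status as a covariate. Enter baseline SSB/juice intake once: either as the baseline response in the mixed model, or as a covariate in a model of the 3- and 6-month values, but not both.
- State that no post-randomisation variable enters the primary model. Follow-up values of the targeted constructs belong in a separate mediation analysis.
- Label any other baseline adjustment, including for imbalance arising from attrition, as a sensitivity analysis.

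The cost is wording and one or two degrees of freedom; all the data are already collected. A gain in precision should be expected only where baseline intake is a covariate for the follow-up values. In a single-outcome analysis with 17 per arm and an assumed R² of .25, power rises from about 81 % to 89–90 %. By check A, childcare status as a main effect in the three-visit model will not move the group-by-time estimate with complete data; including it keeps the analysis in line with the randomisation.

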## Discussion

This study was designed to determine whether a low-burden intervention delivered using mobile methods and targeted towards mothers could be effective at changing child sugar-sweetened beverage intake. There is a critical gap in the literature such that few interventions have been successful at modifying parent and child weight-related behaviors. This is the first randomized controlled trial intended to determine the efficacy of an innovative mobile-based program to change behavior in mother-child dyads.

Though the study is innovative in its design and goals, there are several limitations. First, in order to limit measurement burden on mothers, the outcome of SSB/juice intake was measured by a 1-day 24-h dietary recall, versus the gold standard of 3days of dietary recall data. This is a limitation, as SSB/juice intake likely varies considerably from day to day. However, because the dietary recall data was being used to compare average dietary values between groups, intra-individual variability is less of an issue. Thus, the use of only one dietary recall in this study was the best choice for dietary and SSB/juice assessment in this population. Additionally, the self-reported nature of the SSB/juice and dietary data could be a potential limitation of the study, although use of the 24-h recall is the current standard in behavioral interventions, and research assistants were blinded to treatment group in order to mitigate the risk of bias.

Lastly, this intervention targeted solely an overweight or obese mother as the agent of change due to the well-known strength of association between child and maternal weight and dietary behaviors. However, the intervention did not directly target or involve any other family members living in the home, including fathers, partners, and other children. If the father is overweight or obese [47], and if there are additional children in the home who potentially increase parental barriers to making dietary and physical activity changes, then it may not be sufficient to target only the mother while overlooking the other family members.

Nonetheless, the innovative nature of the Smart Moms intervention will be informative for the literature. Given the rising proportion of preschoolers who are obese, and given that overweight and obese parents could benefit from programs targeted to the demands of having a family, there is a significant need for sustainable interventions that are effective and maximize adherence among parents. Smart Moms adapts the traditional behavioral weight loss intervention to focus on specific dietary behaviors, uses simplified self-monitoring, and delivers intervention materials via technology to reduce time demands and increase parental adherence. Thus, it will contribute to the emerging evidence base seeking to inform successful strategies to prevent childhood obesity through family-based approaches.

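### Comparing group means keeps a one-day recall unbiased but does not protect precision; adjusting for the baseline recall would recover precision at no cost

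*Protocol article*

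**What the plan says.** In the protocol article, Sample size and statistical analysis defines the endpoint as a change: "The primary outcome for the study was change in child SSB/juice intake in fluid ounces from baseline to 6 months". The same section says that "the study was powered to detect a difference of a 6-oz reduction between groups at 6 months". The spread assumed for that comparison is given only by the phrase "with a within-group standard deviation of 6.0". From these inputs, at 80% power, alpha .05 and 20% attrition, the section concludes that "the study required 21 participants per group for a minimum of 42 total participants". The planning values rest on three earlier studies, whose recall method is not described.

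Under Measures, the subsection on beverage intake and diet specifies one 24-hour recall of the child's intake at each assessment.

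Data analysis sets the model: "The linear mixed models will include a random intercept". Group, time and their interaction at both follow-up visits enter as further terms.

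The Discussion concedes that a single recall is a limitation, that intake probably differs a good deal between days, and that three days would be the reference standard. It then argues that "because the dietary recall data was being used to compare average dietary values between groups, intra-individual variability is less of an issue", and concludes from this that one recall was the best option for this population.

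**The concern.** The Discussion's argument runs together two properties of a group mean. Random day-to-day variation does not shift the mean, so a one-day recall is adequate as far as bias goes. It does widen the standard error of the mean, and about 17 completers per group average little of it away.

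The planned analysis makes this matter more. A random intercept removes the stable differences between children from the group-by-time contrast. What remains is variation within a child, and day-to-day variation is a main part of it. The text therefore discounts a source of error that bears directly on the primary test.

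Two things are at stake. A reader may take the one-day measure to cost little and read a null result too firmly. And the planned model gives the noisy baseline recall full weight by testing raw change, although a more precise analysis of the same data is available.

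**Working it through.** **Inputs.** From Sample size and statistical analysis: difference 6 oz, SD 6.0, alpha .05 (two-sided assumed; the article does not say), attrition 20%, 21 per group. Completers per group: 21 × 0.8 = 16.8. The documents give no day-to-day SD and no correlation between visits, so the correlation rho is varied as an assumption. All power figures are noncentral-t values for two means, before the Bonferroni adjustment mentioned in Data analysis.

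**1. The plan's own figure.** The normal approximation gives n = 2 × (1.96 + 0.84)² × 6² / 6² = 15.7, so 16 per group; 16 / 0.8 = 20. The t-based calculation gives 17 per group (power 81%); 17 / 0.8 = 21.25. The stated 21 reproduces. At 16.8 completers and SD 6.0, power is 80%.

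**2. What sets the standard error.** Write the variance at one visit as σ² = σ²(between) + σ²(residual), with rho = σ²(between) / σ². In the random-intercept model,

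Var(change) = 2 × σ²(residual) = 2σ²(1 − rho).

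The between-child part drops out. The residual holds day-to-day variation and any true differences in change between children. If 6.0 is the SD of change, the residual SD that goes with it is 6 / √2 = 4.24 oz.

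**3. Readings of SD 6.0.**
- If 6.0 is the SD of change between single-day recalls, the 80% stands.
- If 6.0 is the SD at one visit, the SD of raw change is 6 × √(2(1 − rho)). Adjusting for baseline gives a residual SD of 6 × √(1 − rho²).

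| rho (assumed) | SD of raw change | Power, raw change | SD, baseline-adjusted | Power, adjusted |
|---|---|---|---|---|
| 0.2 | 7.59 | 60% | 5.88 | 82% |
| 0.3 | 7.10 | 66% | 5.72 | 84% |
| 0.4 | 6.57 | 73% | 5.50 | 87% |
| 0.5 | 6.00 | 80% | 5.20 | 90% |
| 0.6 | 5.37 | 88% | 4.80 | 94% |

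**4. Gain from adjustment under either reading.** The variance ratio, adjusted to raw change, is (1 − rho²) / (2(1 − rho)) = (1 + rho) / 2. It equals 0.60 at rho 0.2, 0.65 at 0.3, 0.70 at 0.4 and 0.75 at 0.5. It depends only on rho (with equal variances at the two visits), so the gain does not hinge on what 6.0 describes.

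**The case against.** The Discussion sentence is comparative and says nothing about power. It follows an open statement that the single recall is a limitation, and it is correct as far as bias goes. All of this stands. What does not stand is the step from unbiased group means to the conclusion that one recall was the best choice, because that step passes over precision.

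A reader might infer that the 80% power is wrong or that the trial is underpowered. The documents do not support this. The sample size reproduces from its own inputs. The SD of 6.0 is given directly after a change outcome and a difference in reduction, so the SD of change is the natural reading. An article may also leave its derivation to the full protocol. Power below 80% needs 6.0 to be a single-visit SD and rho to be below 0.5, neither of which is shown.

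A reader might also suppose that 6.0 came from three-day averages. If half of the change variance were then day-to-day, the one-day SD would be √(36 × (0.5 + 3 × 0.5)) = 8.49 and power 51%. Nothing in the documents suggests that origin or that share, so the figure should not be relied on.

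Nor is day-to-day variation the whole error term. True differences in change between children are in it too, in a proportion that the documents do not give.

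Finally, recalls and enrolment are described in the past tense, so the design can no longer change. The analysis is still described in the future tense and can.

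**Conclusion.** The Discussion's argument is right for bias and wrong for precision. Day-to-day variation is a main component of the residual that determines the standard error of the primary contrast, and comparing group means does not remove it.

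No error in the stated power is established. It is 80% at 16.8 completers per group if 6.0 is the SD of change between single-day recalls. If 6.0 is a single-visit SD, raw-change power runs from 60% at rho 0.2 to 88% at rho 0.6, and the documents do not fix rho.

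The firm conclusion concerns the analysis. Treating baseline as an outcome in the random-intercept model tests raw change. Adjusting for baseline reduces the variance of the contrast by 25% to 40% at rho 0.5 to 0.2. This assumes equal variances at the two visits, a linear relation to baseline and randomised groups.

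**What to change.** In Data analysis, make the primary estimate the 6-month group difference adjusted for the child's baseline intake, in place of the raw-change group-by-time contrast. Either enter the baseline recall as a covariate, or keep baseline in the mixed model with its mean constrained equal across arms. If 6.0 is the single-visit SD, this gives about 82% to 90% power at rho 0.2 to 0.5. Baseline intake is already a stratification factor, so adjusting for it fits the design. The section's confounder rule does not secure this, because it admits only characteristics associated with both treatment group and outcome.

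In the Discussion, replace the group-means argument with a statement that one-day recalls leave group means unbiased but cost precision.

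The cost is a change to the model specification, best made before outcome data are examined, and one reworded sentence. No extra recalls or participants are needed.
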